### Recruitment

Fifty participants will be recruited through the Hospital of the Federal University of São Paulo (Hospital São Paulo) located in São Paulo State, Brazil. Those interested in participation will undergo a detailed screening using the eligibility criteria for enrolment in the study. The sample size was calculated using a statistical software (G^*^Power 3.1.5) on the main outcome measure (i.e., the motor score). This calculation was based on data from five patients (pilot study). The power was 0.80; the α was 0.05, and the effect size was 0.65 (Cohen *d*). The sample estimation indicated that 40 participants would be necessary (i.e., 20 per group), and with an adjustment to allow for a withdrawal rate (20%), we will recruit 50 participants.

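### The sample size of 40 (20 per group) is not reproduced by its stated inputs: the two-group reading gives 52% power, and the crossover reading depends on an unstated correlation

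*Protocol article*

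**What the plan says.** All the inputs are in the Recruitment section of the protocol article.

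- Design values: "The power was 0.80; the α was 0.05, and the effect size was 0.65", described as a Cohen d.
- Source of the effect: "This calculation was based on data from five patients (pilot study").
- Variable sized: "on the main outcome measure (i.e., the motor score").
- Result: "The sample estimation indicated that 40 participants would be necessary (i.e., 20 per group").
- Inflation: "with an adjustment to allow for a withdrawal rate (20%), we will recruit 50 participants".

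The software is named. The test, the sidedness, the SD on which d is standardised and the within-patient correlation are not.

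Three other places bear on how to read the figure. The Overview of the Study Design describes a crossover in which everyone receives both therapies each day, so groups A and B differ only in order. The Statistical Analysis section plans a comparison between groups, labelled virtual and conventional, as well as a comparison within patients. The primary outcome is functional capacity in Table 2, autonomic change in the Primary Outcome section, and the motor score in Recruitment.

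**The concern.** A number per group next to a Cohen d reads as a two-sample calculation. For that test, 20 per group is about half of what d = 0.65 requires. The design is a crossover, however, and a paired calculation with the same 0.65 usually gives a much smaller total than 40. So the stated result matches neither usual calculation.

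This matters because a reader will attach the stated 80% to whichever test is reported, and the plan includes both kinds. If the test is between groups, the real figure is near one half. If it is within patients, the figure is somewhere between 81% and nearly 100%, depending on a correlation that is not given. A null result could not be interpreted without knowing which applies.

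**Working it through.** **Inputs.** From Recruitment: effect 0.65, alpha 0.05, power 0.80, stated result 40 (20 per group), withdrawal 20%. Sidedness is not stated, so both were tried. Power is from the noncentral t distribution.

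**1. Withdrawal step.** 40 / (1 − 0.20) = 50. This reproduces.

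**2. Two independent groups.** With n per group, the noncentrality is d × √(n/2) on 2n − 2 degrees of freedom.

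At n = 20: 0.65 × √10 = 2.055, against a two-sided critical value of 2.024 on 38 df.

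| Reading | Needed per group | Power at 20 | Power at 25 |
|---|---|---|---|
| Two-sided | 39 (78 in total) | 51.7% | 61.5% |
| One-sided | 30 (60 in total) | 64.6% | 73.3% |

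The two-sided test at 20 per group reaches 80% power only for d = 0.91. Neither row gives 20 per group.

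**3. Within-patient comparison, 0.65 read as dz.** The noncentrality is dz × √N on N − 1 df. This needs N = 21 two-sided (80.9%) or 17 one-sided. At N = 40 the two-sided power is 98.0%. Neither total is 40.

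**4. Within-patient comparison, 0.65 standardised on the between-patient SD.** Here dz = 0.65 / √(2(1 − ρ)), where ρ is the correlation between a patient's two measurements. Two-sided:

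| ρ (assumed) | dz | N needed | Power at N = 40 |
|---|---|---|---|
| 0 | 0.460 | 40 | 80.9% |
| 0.1 | 0.484 | 36 | 84.8% |
| 0.2 | 0.514 | 32 | 88.7% |
| 0.3 | 0.549 | 28 | 92.3% |
| 0.5 | 0.650 | 21 | 98.0% |
| 0.7 | 0.839 | 14 | 99.9% |

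Only ρ = 0 returns 40. The row for ρ = 0.5 is the same as reading 0.65 as dz.

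**5. Paired test run separately inside each group.** This needs 21 per group, and 20 gives 78.7%. It is close to the stated number, but a change within one sequence group is not the contrast of VR with conventional therapy.

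**6. What 40 completers can detect within patients.** Solving for 80% power, two-sided, gives dz = 0.454. This does not depend on what 0.65 meant.

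**7. The pilot.** If 0.65 is an observed dz from five patients, then t = 0.65 × √5 = 1.45, and inverting the noncentral t on 4 df gives a 95% interval for dz of −0.36 to 1.60.

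**8. The outcome.** Motor score is not defined. The Motor Function section lists the Barthel Index, TUG and MRC. Table 1 schedules these at the start, at day 8 and after discharge, so by the second assessment each patient has had both therapies. If the motor score is one of them, it cannot supply the within-patient contrast of steps 3 and 4. By contrast, the Assessment Protocol section has the Borg scale, oxygen saturation, respiratory rate and heart rate taken before and after each intervention.

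**The case against.** The strongest reply is that 40 can be obtained. A crossover with d on the between-patient SD and zero correlation needs exactly 40, with 80.9% power, and that splits into 20 per sequence. A five-patient pilot could hardly estimate a correlation, so zero might be a deliberate conservative choice. A paired test within each group also comes close. On this view the fault is a reporting gap in a condensed article, and the 52% applies only to a comparison of orders that does not answer the treatment question.

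Much of this stands. A reader might infer that 40 is impossible; the zero-correlation case shows that it is not. A reader might infer that the crossover needs only 21 patients and has 98% power; that holds only if 0.65 is dz, which the section does not say. A reader might also infer that the trial has coin-toss power for VR against conventional therapy; the 52% belongs to group A against group B, which compares order.

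The reply does not remove the point. Zero correlation is nowhere stated, and it assumes that two measurements on one patient are unrelated, which gives up the main advantage of a crossover. The documents cannot distinguish that route from a slip such as taking the 39 per group of a parallel design as the total. Nor is this detail simply left to a fuller document: the article prints inputs and a result that do not agree under the usual readings, and it still plans a between-group test.

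**Conclusion.** The point holds in conditional form. From the printed inputs, 40 does not follow for a two-group t test or for a paired test with dz = 0.65, one- or two-sided. For the group comparison, power at d = 0.65 is about 52% with 20 per group and 61% with 25 per group, two-sided. For the within-patient comparison at N = 40, power is 80.9% at zero correlation, 92.3% at 0.3 and 98.0% at 0.5; these correlations are assumptions, since none is given.

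The documents do not support saying that 50 recruited is too few. Within patients, 40 completers meet 80% power at any correlation from zero upwards if 0.65 is right, provided that the outcome is measured separately for each therapy. Whether 0.65 is right is another matter: it rests on five patients and, read as an observed dz, is compatible with anything from no benefit to a very large one. The remark on the timing of the motor score rests on its being Barthel, TUG or MRC, which is likely but not stated.

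**What to change.** Keep 50 recruited and rewrite the calculation.

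1. Name one outcome for sizing, measured around each session, and make it agree with the primary outcome in Table 2, Recruitment and the Primary Outcome section. If heart rate variability is chosen, reconcile its timing: the Procedure section has it before each therapy, Table 1 only on days 1 and 8 and after discharge.
2. State the power for the within-patient contrast. Suggested wording: *40 completers give 80% power, two-sided alpha 0.05, for a within-patient standardised difference (dz) of about 0.45.* (The exact value is 0.454.) Add why a difference of that size is worth detecting, because the figure is worked back from N.
3. State the test and sidedness, whether 0.65 is d or dz, and the correlation assumed. Do not claim 98% power for 0.65 unless it is confirmed to be dz.
4. Remove the per-group number as the basis for power. It may stay as the size of each sequence group.
5. If a group A versus group B test is kept, state that it compares order, not treatment, and has about 52% power at d = 0.65 with 20 per group.

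The power statement costs wording only and no patients. If the outcome chosen is not yet recorded at each session, there is also the cost of recording it.

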### Inclusion Criteria

Participants will be included in the study if (1) they are aged between 18 and 90 years; (2) they are diagnosed as having COVID-19 by reverse transcription–polymerase chain reaction, immunoglobulin M, and immunoglobulin G (Corman et al., 2020; Zhong et al., 2020); (3) they are undergoing physical therapy during their hospitalization; and (4) they are able to sign consent form.

### Exclusion Criteria

Participants will be excluded if (1) they do not understand the tasks—the understanding of the task will be evaluated through five attempts at each task in VR; (2) they do not want to use VR; (3) they are not in a physical condition to practice a motor task; (4) the use of an intravenous device makes it impossible to move the arms; (5) they have cardiac arrhythmias and an atrioventricular block or cardiac pacemaker; (6) they have congenital anomalies such as congenital heart defects or pulmonary malformations; and (7) they use drugs that interfere with autonomic nervous systems (ANSs), such as antiarrhythmic agents.

### Withdrawal Criteria

Participants will be withdrawn from the study if they are not willing to continue.

### Randomization

Participants will be randomly allocated to either Group A or Group B with a 1:1 allocation defined by a website (randomization.com). As we will have the participant's characteristics, immediately after the randomization the age and functional capacity (Barthel Index) will be compared between groups. If the groups are not homogeneous, a new randomization will be carried out. This protocol will be repeated until there is no difference between age and Barthel Index among groups (in a maximum of first three attempts at randomization, we always have homogeneous groups). Randomization will be under the control of a blinded investigator who will be the only person allowed to manage the electronic security file of the randomization to locate the individuals. The investigator applying the interventions will then be informed about which group the participant was allocated to so they can conduct the protocol in the correct order of interventions.

### Assessment Scales

We will use functional capacity, muscle strength, mood, enjoyment, satisfaction scales, and physiological assessment, which will be presented as follows:

#### Motor Function

For functional capacity, the following tests will be used: Barthel Index, Timed Up and Go (TUG), and Medical Research Council (MRC).

##### Barthel Index

The Barthel Index is a 10-item instrument measuring functional independence in personal activities of daily living—it reaches a score of 100. The Barthel Index is quick and easy to complete. The scoring instructions used for the Barthel Index have been modified to make the contribution of cognitive problems to functional dependency more explicit. The topics evaluated are as follows: (1) feeding, (2) moving from wheelchair to bed and return, (3) personal toileting (grooming), (4) getting on and off toilet, (5) bathing self, (6) walking on a level surface, (6a) propelling a wheelchair, (7) ascending or descending stairs, (8) dressing and undressing, (9) controlling bowels, and (10) controlling bladder. The Barthel Index has been shown to be appropriate for the assessment of patients' changes over time (Novak et al., 1996; Houlden et al., 2006; Eichhorn-Kissel et al., 2011).

##### Timed Up and Go

The TUG test is a reliable, cost-effective, safe, and time-efficient way to evaluate overall functional mobility. The TUG may be used to assess and monitor physical activity in younger adults, especially those with physical and mental health risk factors. A sturdy armchair with a back will be placed at the end of a hallway or an area with space to perform the test. A piece of tape will be placed on the floor 3 m away from the front edge of the chair. Patients will be seated in the chair with back against the chair back, arms resting on the armrests, and given instructions on how to complete the task, including walking at a normal (rather than rapid) speed. The TUG will require patients to stand up out of the chair, walk 3 m, turn around, walk back to the chair, and sit down. Patients will be given the following instructions: “Stand up on the word ‘go,' walk to the tape, turn around, walk back to the chair, and sit down.” The timing of the test will begin at the word “go” and end when the participant is seated. Patients will perform the test one time; if a clear error is made, they will be asked to repeat the TUG. The dependent variable will be the test execution time (Bohannon, 2006; Herman et al., 2011; Kear et al., 2017).

##### Medical Research Council

This is an instrument adapted to assess muscle strength in critically ill patients. The result is obtained through the evaluation of six movements of upper limbs and lower limbs, and the strength is graded between 0 (plegia) to 5 points (normal strength). The maximum score is 60 points; values of <48 may indicate that the patient has muscle weakness (Craig et al., 2008; Schefold et al., 2020).

#### Mood, Enjoyment, and Satisfaction Scales

For mood, enjoyment, and satisfaction, the following tests will be used: Brunel Mood Scale (BRUMS), Enjoyment Scale (ES), and Visual Analogical Satisfaction Scale (VASS).

##### Brunel Mood Scale

This scale was developed to allow a quick measurement of the mood of adults and adolescents. BRUMS contains 24 simple mood indicators, such as feelings of anger, disposition, nervousness, and dissatisfaction that are noticeable by the individual being assessed. The evaluated responds to the scale according to how they feel about such sensations. The score is 5 points (0 = nothing to 4 = extreme). The question format is “How do you feel now,” although other forms: “How have you felt this past week, including today” or “How do you normally feel” can be used. BRUMS takes about 1 to 2 min to complete. The 24 indicators of the scale comprise six subscales: anger, confusion, depression, fatigue, tension, and vigor (Rohlfs et al., 2008; Sties et al., 2014).

##### Enjoyment Scale

An enjoyment scale using smiley faces (0 is “not fun at all,” 1 is “boring,” 2 is “a bit of fun;” 3 is “fun,” and 4 is “great fun”) will be applied after the end of the game sequences, as the motivation may be related to the motor proficiency level.

This scale was developed by Jelsma et al. (2014) to evaluate how people feel when interacting with proposed non-immersive VR games. It was used in other studies using different games (Farhat et al., 2016; Smits-Engelsman et al., 2017) and by da Silva et al. (2020a) with the same game used in this study. In the present study, the scale will be applied in the first and last days of the protocol to verify the participant's level of satisfaction with the games presented.

##### Visual Analogical Satisfaction Scale

The 10-cm VASS assesses the level of satisfaction of the interviewed individuals. Patients will answer the questionnaire and be asked to mark a vertical line on the scale indicating satisfaction with rehabilitation, where zero (0) indicates very dissatisfied, and 10 indicates very satisfied (Brokelman et al., 2012; Voutilainen et al., 2016).

#### Physiological Assessments

For physiological assessment, the following tests will be used: The Borg Rating of Perceived Exertion (Borg Scale), heart rate variability (HRV), oxygen saturation (Spo_2_), respiratory, and HR.

##### The Borg Rating of Perceived Exertion

The Borg Scale is a tool for monitoring the intensity of physical effort; it is one of the most useful instruments for the evaluation and quantification of the sensations of physical effort, also known as RPE. This is used both in the areas of high-performance sports and physical rehabilitation to monitor the changes caused by physical exercise in the cardiorespiratory, metabolic, and neuromuscular systems (Zamunér et al., 2011; Williams, 2017).

##### Heart Rate Variability

We will use HRV to analyze ANSs before, during, and after the intervention for recovery assessment. The analysis will follow the guidelines of the (Heart rate variability: standards of measurement, physiological interpretation and clinical use. Task force of the European Society of Cardiology and the North American Society of pacing and electrophysiology, 1996). The strap (for data collection) will be positioned on the participant's chest, and the Polar V800 (Polar Electro, Finland) HR receiver will be positioned next to it. HRV will be recorded after the initial assessments at rest for 20 min. For analysis of HRV data at rest, 1,000 consecutive resting rate intervals will be used (da Silva et al., 2018; Moraes et al., 2019). Heart rate will be recorded beat by beat throughout the protocol by the Polar V800 HR receiver, and resting rate intervals recorded by the monitor will be transferred to the Polar ProTrainer program, which allows HRV visualization and cardiac period extraction in the “txt.” file format.

Moderate digital filtering will be performed in the program itself. HRV analysis will be performed using linear (time and frequency domain) that will be analyzed using Kubios HRV® software (Kubios HRV v.1.1 for Windows, Biomedical Signal Analysis Group, Department of Applied Physics, University of Kuopio, Finland) and non-linear methods (Vanderlei et al., 2009).

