**PHYSIOLOGICAL ASSESSMENT**												
Heart rate variability (HRV)			X							X	X	X
The Borg Rating of Perceived Exertion (Borg scale)			X	X	X	X	X	X	X	X	X	X
Oxygen saturation (Sao_2_)			X	X	X	X	X	X	X	X	X	X
Respiratory rate (RR)			X	X	X	X	X	X	X	X	X	X
Heart rate (HR)			X	X	X	X	X	X	X	X	X	X

**Table 2 T2:** Trial characteristics based on WHO Trial Registration Data Set.

**Data category**	**Trial information**
Primary registry and trial identifying number	ClinicalTrials.gov, ID: NCT04537858
Date of registration in primary registry	01 September 2020 on
Secondary identifying numbers	Ethics Committee of the Federal University of São Paulo, under the number CAAE: 33244620.5.0000.5505
Source(s) of monetary or material support	Coordenação de Aperfeiçoamento de Pessoal de Nível Superior–Brasil
Primary sponsor	University of São Paulo
Secondary sponsor(s)	NA
Contact for public queries	[name], [name]
Contact for scientific queries	[name], [name]
Public title	Conventional intervention and non-immersive virtual reality in COVID-19
Scientific title	Comparison Between Benefits of Conventional Intervention and Non-immersive Virtual Reality in the Rehabilitation of Individuals in an Inpatient Unit for the Treatment of COVID-19: A Study Protocol
Country of recruitment	Brazil
Health condition(s) or problem(s) studied	COVID-19
Interventions	Group A: Subjects will start the first day of the protocol with virtual reality intervention and then in the second period will perform the conventional intervention. Group B: Subjects will start the first day with conventional intervention and in the second period will perform activity with virtual reality intervention. Both therapies will be performed on the same day at different times for 10 consecutive days

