### Assessment Protocol

The assessment protocol will have the following sequence. The functional scale (Barthel Index) will be undertaken first to ensure balance in randomization as this is a key variable. This is followed by group randomization process. After that, assessment scales will be undertaken in a separate room (BRUMS, MRC, and TUG) and one physiological assessment (HRV). The assessment part of the protocol will take around 1 h.

Borg Scale, Spo_2_, RR, and HR will be evaluated before and after each intervention. At the end of each day, ES and VASS questionnaires will be used to determine the individual's final perception of the intervention.

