### Procedure

Immediately before the beginning of each therapy (virtual intervention or conventional intervention), two assessment scales will be made (BORG Scale, Visual Analog Scale) and four physiological assessments [HRV, Spo_2_, RR, and HR]. Group A will start the first day of the protocol with virtual intervention (in the morning) and then in the second period (in the afternoon) will perform the conventional intervention, and Group B will perform the reverse protocol, in a crossover format. It will be applied for up to 8 consecutive days. On the last day, assessment scales will be repeated in a separate room, as well as the physiological assessments. After 7 days and 1 month of hospital discharge, all assessment scales will be undertaken at patients' homes, and the virtual intervention will be applied again (Figure 2).

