### Primary Outcome

We will observe changes in the ANSs after intervention with VR and conventional therapy in inpatients with COVID-19, during hospitalization and after 7 and 30 days of follow-up after hospital discharge.

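### The protocol times HRV in four different ways, and only one of them could give a before-and-after autonomic change for each therapy

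*Protocol article*

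**What the plan says.** The Primary Outcome section of the protocol article states: "We will observe changes in the ANSs after intervention with VR and conventional therapy in inpatients with COVID-19". It extends this over the hospital stay and to 7 and 30 days after discharge. Four places then say when HRV is taken:

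- **Heart Rate Variability section:** "We will use HRV to analyze ANSs before, during, and after the intervention for recovery assessment". It adds: "Heart rate will be recorded beat by beat throughout the protocol by the Polar V800 HR receiver". The one resting record it specifies is at the start: "HRV will be recorded after the initial assessments at rest for 20 min".
- **Table 1, physiological assessment:** HRV is marked at t1, t8, t9 and t10 only. Borg, oxygen saturation, respiratory rate and heart rate are marked at every time point from t1 to t10.
- **Assessment Protocol:** HRV appears once, in the initial assessment. The next paragraph reads "Borg Scale, Spo_2_, RR, and HR will be evaluated before and after each intervention", and HRV is not in that list.
- **Procedure:** "Immediately before the beginning of each therapy (virtual intervention or conventional intervention), two assessment scales will be made", together with "four physiological assessments [HRV, Spo_2_, RR, and HR". The physiological assessments are repeated once, on the last day.

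The Overview of the Study Design and the Interventions row of Table 2 give both therapies to every patient on the same day. The Overview and the Intervention section set the treatment period at 2 to 8 days.

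**The concern.** The randomised groups differ only in the order of the two therapies. A change from day 1 to the last day, or to follow-up, therefore carries the effect of both and cannot be assigned to either. Evidence about one therapy has to come from HRV tied to a session of that therapy. Whether such readings exist depends on which part of the protocol the evaluator follows, and evaluators following different parts would collect data that cannot be pooled.

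The outcome matters under either label the article gives it. The Primary Outcome section makes autonomic change primary, while Table 2 lists functional capacity as primary and HRV as key secondary. That is a separate conflict.

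**Working it through.** The plan gives no figure to reproduce here. The check is to count, for each source, the HRV readings tied to a session and see whether a pre/post pair results.

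Inputs: 2 sessions per day, one of each therapy (Overview of the Study Design); 2 to 8 treatment days (Overview, Intervention).

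Sessions per patient = 2 × days, so 2 × 2 = 4 up to 2 × 8 = 16.

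| Source | In-hospital HRV | Stated before a session | Stated after a session | Pre/post pair per session |
|---|---|---|---|---|
| Heart Rate Variability section, read per session | 3 × 4 = 12 to 3 × 16 = 48 segments | 4 to 16 | 4 to 16 | Yes, but post window undefined |
| Table 1 | 2 marked days (t1, t8) | none identified | none identified | No |
| Assessment Protocol | 1 initial reading | 0 per session | 0 | No |
| Procedure | 4 to 16, plus 1 on the last day | 4 to 16 | 0 | No |

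Three details bear on how these are read.

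1. Table 1 ties the end-of-treatment mark to day 8. Read literally, a patient treated for fewer than 8 days has one in-hospital HRV day, and 3 marked readings in all instead of 4. The Procedure's last-day wording avoids this.
2. Under the Procedure, the afternoon pre-session reading could serve as a delayed value after the morning session. The afternoon session's next reading is the following morning, so the two therapies would not be measured alike within a patient. On day 1 the morning-to-afternoon change could be compared between Groups A and B. That would be a between-patient comparison of whatever effect remains after an unstated interval, not a change around the session.
3. In the Heart Rate Variability section, the intervention may mean each session or the whole hospital course. Only the first meaning gives a value per therapy. The resting record and the 1,000-interval rule are both stated for rest, and no rest period after a session is described.

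**The case against.** The strongest reply is that the sources can be read together. Table 1 has day columns only, so it cannot show a pre/post split for any measure: oxygen saturation, respiratory rate and heart rate carry plain marks there, yet other sections take them before and after each therapy. The Procedure also mentions only the pre-session reading for those measures. HRV before, during and after sessions on day 1 and the last day would fit both Table 1 and the Heart Rate Variability section. Recording is said to run throughout, and HRV during VR against HRV during conventional therapy is also specific to one therapy. Figure 2 is not shown and may place HRV more exactly.

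Much of this stands. A reader might infer that autonomic change cannot be computed per therapy at all. The documents do not support that, because the Heart Rate Variability section, read per session, would allow it. A reader might also fault the 1,000-interval rule because a beat count spans different times at different heart rates. The rule is stated for rest and no text applies it after exercise, so it is not an error as written. Nor is this a multi-site problem: recruitment is at one hospital.

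What the reply does not remove is the difference between HRV and its companions. For oxygen saturation, respiratory rate, heart rate and Borg, another section supplies the reading after each session. For HRV, the Assessment Protocol omits it from exactly that list, and the Procedure's reading before every therapy does not fit two marked in-hospital days. These are incompatible statements, which is different from an article leaving detail to a fuller document.

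**Conclusion.** The concern holds as an inconsistency with a defined consequence. Under Table 1, the Assessment Protocol or the Procedure as written, no pre/post HRV change per therapy is available: 0 of the 4 to 16 sessions has a stated reading after it. Under the Heart Rate Variability section, every session could have one, provided the intervention there means each session and a post-session window is defined.

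This rests on taking HRV as the measure of the autonomic outcome, as the article does, and on both therapies being given each treatment day. It does not depend on whether HRV is finally labelled primary or key secondary. The matter is worth settling promptly: Table 2 gives the status as recruiting, and a resting segment that was never taken cannot be recovered at analysis.

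**What to change.** Reconcile Table 1, the Heart Rate Variability section, the Assessment Protocol and the Procedure on one HRV schedule:

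- At least on day 1 and the last treatment day, take HRV before and after each VR session and each conventional session. Replace the fixed day-8 mark with the last treatment day.
- Use short windows of equal duration, in the same posture, drawn from the beat-by-beat recording already planned, and state where the post-session window begins.
- Make VR versus conventional within-session change the per-therapy comparison in hospital.
- Keep the 7- and 30-day values as follow-up, described as reflecting both therapies together.
- For patients already treated, record which schedule was followed and whether the recording ran on after each session.

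The minimum is 2 days × 2 sessions × 2 windows = 8 windows per patient. Four of these are the pre-session readings that the Procedure already calls for. Covering every session would take 2 × 4 = 8 up to 2 × 16 = 32 windows, which is why day 1 and the last day are the practical minimum. The cost is revised wording, a revised Table 1 row and a few minutes of quiet rest around the measured sessions. The windows must be short to keep it that low, since each motor session is only 10 minutes.
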